## Abstract

**Background:**

Driving is a complex behavior that may be affected by early changes in the cognition of older individuals. Early changes in driving behavior may include driving more slowly, making fewer and shorter trips, and errors related to inadequate anticipation of situations. Sensor systems installed in older drivers’ vehicles may detect these changes and may generate early warnings of possible changes in cognition.

**Method:**

A naturalistic longitudinal design is employed to obtain continuous information on driving behavior that will be compared with the results of extensive cognitive testing conducted every 3 months for 3 years. A driver facing camera, forward facing camera, and telematics unit are installed in the vehicle and data downloaded every 3 months when the cognitive tests are administered.

**Results:**

Data processing and analysis will proceed through a series of steps including data normalization, adding information on external factors (weather, traffic conditions), and identifying critical features (variables). Traditional prediction modeling results will be compared with Recurring Neural Network (RNN) approach to produce Driver Behavior Indices (DBIs), and algorithms to classify drivers within age, gender, ethnic group membership, and other potential group characteristics.

**Conclusion:**

It is well established that individuals with progressive dementias are eventually unable to drive safely, yet many remain unaware of their cognitive decrements. Current screening and evaluation services can test only a small number of individuals with cognitive concerns, missing many who need to know if they require treatment. Given the increasing number of sensors being installed in passenger vehicles and pick-up trucks and their increasing acceptability, reconfigured in-vehicle sensing systems could provide widespread, low-cost early warnings of cognitive decline to the large number of older drivers on the road in the U.S. The proposed testing and evaluation of a readily and rapidly available, unobtrusive in-vehicle sensing system could provide the first step toward future widespread, low-cost early warnings of cognitive change for this large number of older drivers in the U.S. and elsewhere.

## Background

About 1 in 9 (10.7%) people in the US age 65 and older has Alzheimer’s disease or related dementia; another 15 to 20% have mild cognitive impairment (MCI), and one-third of these will develop dementia within 5 years [1]. Older African Americans and Hispanics have a higher prevalence rate, probably related to higher rates of diabetes, cardiovascular disease, and the effects of socioeconomic disadvantage [2], reinforcing the importance of culturally diverse samples in Alzheimer’s research. Individuals with dementia eventually cannot perform complex everyday activities, including driving. Interestingly, the neuropathologies of AD (Alzheimer’s Disease) have been found in the brains of older drivers killed in motor vehicle accidents who did not even know they had AD and had no apparent signs of it [3].

Older drivers may be at greater risk of collision in the years before AD diagnosis [4]. One analysis identified a five-fold increase in crashes 3 years before the diagnosis of dementia and a higher likelihood of failing a road test (risk ratio = 10.77) [5]. Similarly, Fraade‐Blanar and colleagues [6] found that a one unit-lower Cognitive Abilities Screening Instrument scored using item response theory (CAS-IRT) predicted a crash incidence rate of 1.25 in a sample of 2,165 older group health enrollees. Drivers with dementia make twice as many mistakes as controls and fail on-the-road tests at a rate of 67% compared to 3% for controls [7]. Pavlou and colleagues [8] reported that driving behavior changes such as speed, lateral position, reaction time, following distance, left turns, and time off the road distinguish normal controls from those with cerebral pathologies.

Previous research has focused on older drivers with dementia, but interest in the driving behavior of individuals with MCI is increasing. Few studies have reported the use of continuous, unobtrusive sensors and related monitoring devices for detecting subtle variability in the performance of highly complex everyday activities over time. Eby and colleagues [9] employed in-vehicle technology to monitor driving performance for 2 months. Compared with 26 unimpaired drivers, 17 drivers with early-stage dementia were found to have significantly restricted driving space and were more likely to get lost, even though they had been cleared for driving. In a small sample of 21 unimpaired older adults and 7 with MCI who were followed for 200 days using a sensing device, those with MCI drove fewer miles and fewer of these miles on highways [10].

The Long Road study (2021) is among the first longitudinal studies showing the usefulness of naturalistic data and machine learning techniques to detect MCI and dementia from driving behavior [11]. Among 2977 older drivers studied, 64 were identified as having MCI or dementia through a review of their medical records and annual interview. Age was predictive of MCI and dementia, followed by the percentage of trips traveled within 15 miles of home, race/ethnicity, minutes per trip chain (i.e., length of trips starting and ending at home), minutes per trip, and the number of challenging braking events with deceleration rates 0.35 g. The point of conversion to MCI or dementia could not be determined, at least partly due to the data collection method. Data from our naturalistic, longitudinal study may contribute to identifying these time points.

Similarly, Bayat and colleagues [12] conducted a study using machine learning methods to evaluate the ability of in-vehicle GPS to distinguish drivers with preclinical AD from those without preclinical AD. Using four Random Forest (RF) models with three sets of variables, driving features only, driving features and age, and driving features, age, andAPOE*ε*4 status, it was found that prediction of preclinical AD was 82% using GPS-based driving indicators, 88% using age and driving indicators, and 91% using age, APOE *ε*4 status, and driving.

Davis et al. [13] performed a pilot study using in-vehicle technology (GPS, video) to capture driving behaviors and errors of adult drivers with preclinical AD and early symptomatic AD compared to cognitively normal adults. In early AD, g-force (a vector of acceleration) events produced common errors predominately related to inadequate anticipation of situations, such as late response or driving too fast, mistakes of judgment, and frequent traffic violations. Davis et al. [13] suggest that an event-based approach rather than costly continuous video monitoring to assess driving risk behaviors can be more efficient. Those with preclinical AD drove more slowly and had the lowest number of aggressive events over 3 months. An important limitation of the study was that cognitively intact individuals (CDR = 0) did not have video installed in their vehicles.

The rationale for the current research arises from the importance of identifying cognitive dysfunction as early and efficiently as possible. An estimated 4 to 8 million older adults with MCI are currently driving [14]. This significant proportion of older drivers constitutes a previously unexplored opportunity to detect cognitive decline. In this study, we will systematically examine how current in-vehicle technologies may detect anomalous driving behavior indicative of cognitive impairment.

## Methods/design

### Objective

The objective of this study is to test an unobtrusive multi-sensor system’s ability to detect cognitive change in older (≥ 65) drivers.

### Aims

To achieve this goal, the In-Vehicle study has the following aims:Test the ability of a package of in-vehicle sensors to detect cognitive change:Establish baseline cognitive status and driving behaviors.Examine sensor data output for the ability to detect the cognitive change in individual measures, latent constructs, and diagnostic groupings (e.g., change from unimpaired to MCI) over time.Identify cognitive changes that in-vehicle sensors can detect.Identify the sensor system components that best predict these significant changes in cognition.Develop algorithms that can:Translate sensor data into Driving Behavior Indices (DBIs) that are gender, age, and vehicle specific.Examine the accuracy and stability of the DBIs by comparing DBIs generated using exponential smoothing and ARIMA techniques to DBIs that are adjusted for weather and road conditions derived from national and state databases.Provide interpretable indicators of change in DBI and associated decline in the underlying cognitive functions.Evaluate the acceptability to older drivers of the installed systems.Evaluate participants’ response to the sensor system in terms of their awareness of the installed system, obtrusiveness, driver distraction, reported effect on driving behavior, and overall acceptability.

### Study design

This study will utilize a naturalistic longitudinal parallel mixed methods design. The quantitative phase of this research will be a longitudinal forecasting design with latent constructs. The qualitative phase will use content analysis to investigate the drivers’ perception of acceptability and the unobtrusive nature of the sensor unit.

### Sample size calculation

The average national percent change in cognition disaggregated by age groups (65–74, 75–84, 85+) over a 3-year period [15] was used to calculate number of participants. G*Power 3.1.9.2. was used to calculate the total number of participants predicted to show measurable change in cognition required to obtain power = 0.80 with an alpha = 0.05, 2 groups (Change, No-Change), 12 repeated measures, a correlation between measures of 0.5 and a medium effect size (Cohen’s f = 0.0.17) which is 200 using the repeated measures algorithm in G*3.1.9.2. With an average of 52.1% of the participants estimated to show a minimum change over the 3-year period, a total sample of 384 participants is required. Due to their age and driving requirements of the participants in this study, a 20% attrition rate [16] was used to calculate the total number of participants to be enrolled in this study. This resulted in a total required sample of 460.

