#### Controlling for practice effects

Important issues in this study of cognitive change are the potential for practice and retest effects in performance on repeatedly administered cognitive tests, a problem common to longitudinal studies. Although we may assume that these effects are observed in all clinical groups, they may not be equivalent across groups.

While there is no clear consensus on the best methods to address this problem, we will address it by:Using alternative forms with equivalent psychometric properties where available. The IDN, ONB, TWOB, and the GMLT are short and repeatable assessments that are unaffected by language, therefore we are able to have a large stimulus set that is controlled and randomized so that each participant has a unique stimulus set at each time point. The AFT uses a set of pseudo randomizations controlling for the number of congruent and incongruent trials.The most prominent practice effects generally take place between the first and the second administration of a test. For this reason, we will use a double baseline design in which the second assessment (3 months after the first) will be used as the baseline for all cognitive measures.In the statistical analysis we will include reliable change indices (RCIs), and regression base analyses with correction for practice effects.

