#### Predictive modeling phase

Two different methods will be used to model the prediction of changes in cognitive functioning followed by a sensitivity analysis. First, a traditional predictive modeling method using a linear mixed effects (LME) model with time varying covariates will be conducted [46]. This LME method will use the processed data aggregated at weekly, monthly, and 3-month intervals along with the features determined by the SHAP analysis. The second method will use a machine learning recurrent neural network (RNN) approach to loop over and pass information from one step to another in the network allowing for the capability to effectively incorporate temporal (time) dependencies in longitudinal data [47]. With RNN, data contains data sequences from k time steps at each time point (ti), input features (Xti), and internal state (memory) from the previous time step (ht(i−1)) allowing for RNN to identify patterns hidden in the sequence of the data not detectible by conventional neural networks [48]. The Driving Behavior Indices (DBIs) algorithms generated will be assessed for ability to predict changes in overall cognitive functioning as well as other specific domains.

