## Discussion

A naturalistic 3-year longitudinal study will be conducted to test the ability of an in-vehicle sensor system of telematic and video sensors to obtain data that can signal a change in the driver’s cognitive status will be tested. The innovation of this research project lies in the unobtrusive, rapidly, and readily available in-vehicle sensing and monitoring system built upon modern open-source hardware and software using existing techniques to develop and customize the components and configure them for this new purpose. We have hypothesized that this system will be capable of detecting a change in cognitive status among older drivers who are developing MCI or exhibiting symptoms of early-stage dementia.

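### The 0.80 power is computed for a Change/No-Change comparison that the described analysis does not contain, so no planned conclusion is shown to have it

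*Protocol article*

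**What the plan says.** All references are to the protocol article.

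- **Sample size calculation.** The number of participants is chosen to "obtain power = 0.80 with an alpha = 0.05, 2 groups (Change, No-Change), 12 repeated measures", with "a correlation between measures of 0.5 and a medium effect size". The effect size and result are printed as "f = 0.0.17) which is 200 using the repeated measures algorithm". The next step is "With an average of 52.1% of the participants estimated to show a minimum change over the 3-year period, a total sample of 384 participants is" needed, and an attrition allowance brings enrolment to 460. The paragraph does not name the outcome compared between the groups, define the minimal change, or say which repeated-measures test was used.
- **Data processing and predictive modeling phases.** Features are selected by elastic net and SHAP. Then "a traditional predictive modeling method using a linear mixed effects (LME) model with time varying covariates will be conducted", followed by a recurrent neural network. Both predict change in cognition from driving features.
- **Controlling for practice effects.** "In the statistical analysis we will include reliable change indices (RCIs") and practice-corrected regression. The indices are not used to form two groups.
- **Discussion.** The hypothesis is that the system can succeed in "detecting a change in cognitive status among older drivers who are developing MCI or exhibiting symptoms of early-stage dementia".
- **Background.** Of people aged 65 and older, about 1 in 9 has dementia and "another 15 to 20% have mild cognitive impairment (MCI), and one-third of these will develop dementia within 5 years".

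**The concern.** A power figure describes one test of one outcome. Here the test behind the 0.80 compares participants who change with those who do not, on 12 occasions. The analysis as described fits two prediction models and makes no such comparison. The event that determines the size, a minimal change in about half the sample, is also broader than the status change named in the Discussion.

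A reader may well take 460 participants to mean 80% power to show that the sensors detect developing MCI or early dementia. That was not computed. If few participants change diagnosis, a null or imprecise result for those transitions could be read as failure of the sensors when it only reflects few events. Meanwhile, the contrast that the sample size does support would go unreported.

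**Working it through.** **1. The plan's own figures.** Inputs from the sample-size paragraph: two groups, m = 12 measures, rho = 0.5, alpha = 0.05, and f read as 0.17 (the printed value has a stray decimal point). For a between-groups repeated-measures test with N participants,

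lambda = N f² m / (1 + (m − 1) rho), with F on 1 and N − 2 degrees of freedom.

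- N = 150: lambda = 150 × 0.0289 × 12 / 6.5 = 8.00, power 0.80.
- N = 200: lambda = 200 × 0.0289 × 12 / 6.5 = 10.67, power 0.90.
- Within-subject or interaction tests with the same f need 26 (epsilon = 1), 40 (epsilon = 0.5) or 127 (epsilon = 1/11).

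None of these gives 200 at power 0.80. The next step does reproduce: 200 / 0.521 = 383.9, so 384. If all 384 were compared as 200 against 184, between-groups power would be 0.99.

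**2. Comparison of the sections.** The sample-size paragraph has two groups defined by change. The predictive modeling phase has a mixed model and a neural network, with no two-group contrast and no definition of change. The reliable change indices are the nearest link, but they appear only under practice effects.

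**3. How many MCI-to-dementia transitions.** This assumes that the Background rates apply to the enrolled sample. Take 15 to 20% with MCI, one-third progressing in 5 years, and scale to 3 years.

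- Linear scaling: 384 × 0.15 × (1/3) × (3/5) = 11.5, and 384 × 0.20 × (1/3) × (3/5) = 15.4.
- Constant hazard: the 3-year risk is 1 − (2/3)^0.6 = 0.216, giving 384 × 0.15 × 0.216 = 12.4 and 384 × 0.20 × 0.216 = 16.6.

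That is about 12 to 17 events, against the 200 changers in the plan.

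**4. Power with that few changers.** Hold the plan's mean difference: f = 0.17 with equal groups is d = 2 × 0.17 = 0.34. With a share p of changers, f² = 0.34² × p(1 − p). Use the between-groups formula with N = 384. N = 368, which is 460 × 0.8, gives nearly the same values.

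| Changers | Power, rho 0.5 | Power, rho 0.7 |
|---|---|---|
| 12 | 0.35 | 0.27 |
| 16 | 0.44 | 0.34 |
| 17 | 0.46 | 0.36 |
| 30 | 0.68 | 0.55 |
| 42 | 0.80 | 0.68 |
| 60 | 0.91 | 0.81 |
| 83 | 0.96 | 0.89 |

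**5. All status changes together.** The article gives no incidence of MCI among the unimpaired. Assuming 2 to 8% per year, the 3-year risk is 1 − 0.98³ = 0.059 to 1 − 0.92³ = 0.221.

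- Low end: 326 unimpaired × 0.059 = 19, plus 12 dementia transitions, is about 31.
- High end: 307 unimpaired × 0.221 = 68, plus 17, is about 85.

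The table shows that this range runs from below 0.80 to well above it. The question is not settled by the document.

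**The case against.** Four points can be made for the plan.

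- **Measurable change is a target of the study.** The objective is to detect cognitive change. Aim 1 lists individual measures and latent constructs along with diagnostic groupings. The cognitive battery is meant in part to pick up subtle change apart from clinical assessment, and the driving indices are to be judged on overall and domain-specific change. This stands. A reader might infer that the sizing contrast lies outside the study's hypothesis, but that follows only if one Discussion sentence is taken as the whole hypothesis.
- **Power may well be adequate.** By the method above it passes 0.80 at about 42 changers (rho 0.5) or 60 (rho 0.7). This stands too. A reader might infer that no planned conclusion has 0.80 power, but the article supports only that none is shown to have it.
- **The low figures depend on assumptions.** The repeated-measures test is unnamed. The same f put into a group-by-time interaction with 14 changers gives 0.996, 0.93 or 0.45 as epsilon falls from 1 to 0.5 to 1/11, although f has a different meaning there. The Background rates describe the general older population, whereas participants are volunteers screened on the MoCA and for neurological disorders. Completed conversion to dementia is also only one part of the hypothesised event. So 0.35 to 0.44 is conditional.
- **An article condenses.** A mixed model is a repeated-measures model, classification of drivers is mentioned in the abstract, and a statistical analysis plan may say how the change indices enter. This limits the point to the analysis as described. It does not remove it, because the article states both a basis for the size and an analysis, and the two do not match.

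**Conclusion.** The concern holds in limited form. The 0.80 belongs to a Change/No-Change repeated-measures comparison that the described analysis lacks. The event used for scaling is broader than the status change in the Discussion. No planned conclusion is therefore shown to have 0.80 power.

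Power for the mixed model and the neural network, and for status change overall, cannot be determined from the article. It would be wrong to read this as proof that the study is underpowered. A shortfall can be illustrated only for MCI-to-dementia transitions: about 12 to 17 events among 384, with power of about 0.35 to 0.44 for 12 to 16 of them. That rests on the Background rates applying to this sample, a between-groups test, d = 0.34 and rho = 0.5.

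Separately, 200 does not follow from the printed inputs at 0.80. With f = 0.17, a between-groups test needs about 150, and 200 gives about 0.90. This does not supply the missing link to the analysis, but it is a further reason to restate the paragraph.

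**What to change.** 1. In the predictive modeling section, add the Change/No-Change contrast that the size was built for. Define Change by the practice-corrected reliable change index already planned, on a measure or composite named in advance, and name the outcome compared between the groups. Assess the mixed model and the neural network against this grouping, alongside the domain-specific outcomes. The measure should not have to be one given at all 13 visits: that would leave the MoCA as the only cognitive test and sideline the executive and attention tests that the battery puts first. The computerised Cogstate tasks, for example, are scheduled at 12 of the 13 visits.
2. Restate the sample-size paragraph for that contrast. Name the G*Power test, print f correctly, and give the N or power that follows (with f = 0.17 and a between-groups test, about 150 for 0.80, or about 0.90 with 200).
3. State that the 0.80 does not extend to transitions to MCI or dementia. Report those as secondary, with confidence intervals.

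The cost is some rewording, one added analysis of data already to be collected, and a less favourable power statement for diagnostic transitions. No extra participants are needed.

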#### Scheduling over 3 years

The project aims to identify cognitive changes over time that may be associated with indicators from the in-vehicle sensors. Therefore, cognitive assessments are administered every 3, 6, and 12 months (depending on the tests) for 3 years, for a total of 13 quarterly assessments. Every 3 months the following cognitive assessments will be administered: MoCA, FAQ, GDS-15, and the DSAQ (Driver Sensor Acceptability Survey which responds to Aim 3 of the study (See list of abbreviations)). The IDN, GMLT, ONB, and TWOB will be administered at every time point except for Visit 1 in order to keep the first visit under 3 h. Since we will use parallel forms of these tests, they do not need a double baseline. The following assessment tools will be administered beginning with Visit 2 and again on Visit 3 for the double baseline, then every 6 months: ECog, BFD, TMT, AFT, SCWT, VF, and MINT. The UFOV will be administered on Visits 1 and 2, then repeated every 6 months. Lastly, the LASSI-L and Craft Story will be administered at visits 1 and 2 for the double baseline and then every 12 months. The MMSE will be administered on visits 1, 5, 9, and 13.

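### The printed sample size of 200 does not follow from the stated inputs, and this two-group total is then used as the size of the Change group alone; on f = 0.17 both slips add power

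*Protocol article*

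**What the plan says.** The Sample size calculation section of the protocol article gives the inputs as "2 groups (Change, No-Change), 12 repeated measures, a correlation between measures of 0.5 and a medium effect size", with "power = 0.80 with an alpha = 0.05". Cohen's f is printed as 0.0.17. The result is a number "which is 200 using the repeated measures algorithm in G*3.1.9.2", and the sentence describes it as the count of participants predicted to show measurable cognitive change. The section does not say whether the between-factors, within-factors or interaction test was chosen, and it does not name the outcome that is measured repeatedly.

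The next step is introduced by "With an average of 52.1% of the participants estimated to show a minimum change over the 3-year period" and leads to 384. A 20% attrition rate then leads to 460.

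**The concern.** The paragraph states its inputs, its software and its result, so a reader should be able to repeat it. Two steps fail. The inputs do not return 200 under any of the standard repeated-measures options. The 200 is also treated as one group, although G*Power returns the total over all groups entered, here Change and No-Change together.

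This paragraph is the article's only justification for enrolling 460 older drivers for quarterly visits over three years. If 200 does not come from the inputs, and 384 is built on a misreading of what 200 counts, the reader cannot tell what effect the study was sized to detect or what power it has.

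**Working it through.** **Inputs, all from the Sample size calculation section.** Power 0.80; alpha 0.05; k = 2 groups; m = 12 measures; correlation rho = 0.5; share expected to change 52.1%; attrition 20%. Assumption: 0.0.17 is read as f = 0.17.

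**The plan's later steps.**
- 200 / 0.521 = 383.9, which rounds up to the printed 384. This shows that 200 was taken as the number of changers.
- 384 × 1.2 = 460.8, printed as 460. Losing 20% of 460 leaves 460 × 0.8 = 368. How attrition was applied is a separate matter; 368 is used here only as the retained sample.

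**Between-factors test.** Noncentrality λ = f²·N·m / (1 + (m − 1)·rho), with 1 and N − 2 degrees of freedom. Here f² = 0.0289 and the denominator is 1 + 11 × 0.5 = 6.5.

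| Total N | λ | Power |
|---|---|---|
| 148 | 0.0289 × 148 × 12 / 6.5 = 7.90 | 0.797 |
| 150 | 0.0289 × 150 × 12 / 6.5 = 8.00 | 0.8025 |
| 200 | 0.0289 × 200 × 12 / 6.5 = 10.67 | 0.902 |
| 368 | 0.0289 × 368 × 12 / 6.5 = 19.63 | 0.993 |
| 384 | 0.0289 × 384 × 12 / 6.5 = 20.49 | 0.995 |

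The smallest even total with power of at least 0.80 is 150, and 13 measures also give 150. The table assumes equal groups. A 52.1:47.9 split multiplies λ by 4 × 0.521 × 0.479 = 0.998, and the power at 368 and 384 is unchanged to three decimals.

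**Within-factors and interaction tests.** λ = f²·N·m·ε / (1 − rho), with (m − 1)ε and (N − 2)(m − 1)ε degrees of freedom.
- ε = 1: N = 26, λ = 0.0289 × 26 × 12 / 0.5 = 18.03, power 0.816.
- ε = 1/11, the lowest possible value: N = 128, λ = 0.0289 × 128 × 12 / (11 × 0.5) = 8.07, power 0.805.
- The alternative effect-size conventions give 54 to 56 for the interaction, and the multivariate interaction test gives 36.

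**Other readings of the misprint, between factors.** f = 0.017 gives 14,714; f² = 0.017 gives 254; partial eta-squared of 0.017 gives 248. None is 200.

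**What would give 200.** For the between-factors test, one change is enough: power 0.90 (0.899 at 198, 0.902 at 200); correlation 0.7 (λ = 0.0289 × 200 × 12 / 8.7 = 7.97, power 0.802); or f of about 0.147 (λ = 0.0216 × 200 × 12 / 6.5 = 7.98, power 0.803).

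**If 200 is right and an input is misprinted.** The retained 368 is still 368 / 200 = 1.84 times that total. With correlation 0.7 or f = 0.147, λ at 368 is about 14.7 and power about 0.97.

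**The 200 as one group.** Since 200 is the total over both groups, its expected split is about 104 Change and 96 No-Change (200 × 0.521 and 200 × 0.479). The plan instead asks for 200 Change, which brings in about 184 No-Change (384 × 0.479).

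**The case against.** The strongest reply is that nothing is lost. Both slips raise the sample size, and the study stays well powered at 368 under harsher inputs: about 0.98 with only 3 measures and 0.95 with correlation 0.8. This stands, and it fixes the direction of the point. A reader told that 0.80 is not the power of this design might infer a shortfall. On f = 0.17 the power is higher than stated, not lower.

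A second reply is that 150 is less firm than it looks. It rests on reading a misprint as 0.17 and on choosing the between-factors test. N is sensitive to f: 0.15 gives 192. This also stands, so 150 is conditional. The mismatch with 200 does not depend on which test is chosen, because with f = 0.17 none of them reaches it.

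A reader might also infer that 12 measures is wrong, because the Scheduling over 3 years section gives many tests less often, for example "beginning with Visit 2 and again on Visit 3 for the double baseline, then every 6 months". The document does not establish this. The repeated outcome is not named. If driving behaviour is compared between groups defined by cognitive change, 13 quarterly visits bound exactly twelve 3-month driving intervals. Some computerised tests are also given at every visit except the first, which is 12 times. If a less frequent test were the outcome, the effect would be modest: 162 with 6 measures and 184 with 3.

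Finally, 0.17 lies between Cohen's conventional small (0.10) and medium (0.25), so the word medium does not fit it. That is minor, since the calculation uses the number. It does remove one way of resolving the misprint: 0.25 would give 70.

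**Conclusion.** The concern holds as a fault of traceability. The printed inputs do not yield 200: the likely reading gives 150, so 200 is a third larger, and the other tests give 26 to 128. A two-group total is then used as the size of one group. The stated 0.80 is therefore not the power at 200 (about 0.90), at 384 (0.995) or at the retained 368 (0.993).

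These figures assume f = 0.17 and the between-factors test. That test fits best, because the inputs listed are the ones it needs and no nonsphericity correction is given, which the other tests would require. The statement that power is ample also depends on f being near 0.17. It would not hold if 0.017 were meant, but that reading needs thousands of participants and cannot lie behind a result of 200.

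The documents do not support calling the study underpowered. Nor do they show which entry is wrong: power 0.90, correlation 0.7 and f of about 0.147 each explain 200, and nothing in the text selects among them. The paragraph must still be corrected, because a stated sample size and power that the inputs do not produce are wrong as written.

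**What to change.** Rewrite the Sample size calculation paragraph.

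1. Name the G*Power test (between factors, within factors or interaction, with the nonsphericity correction where it applies) and the repeated outcome it refers to.
2. Print one value of f, and drop the word medium if that value is 0.17.
3. Re-run the calculation and correct whichever input or result is wrong.
4. State that the resulting N is the total over both groups, and remove the step that treats it as the number of changers.
5. Report the power, or the smallest detectable f, for the retained sample at the expected 52.1:47.9 split. On the present inputs with f = 0.17 this is about 0.99 at 368.
6. Give power separately by number of administrations only if the repeated outcome is a cognitive test given fewer than 12 times.

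The cost is one re-run and a rewritten paragraph. This point requires no change to enrolment, design or visit schedule.

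### The enrolment target of 460 adds 20% to 384 instead of dividing by 0.80, so at the plan's own 20% attrition it leaves 368 participants and about 192 changers, not 384 and 200.

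*Protocol article*

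**What the plan says.** The whole calculation stands in one paragraph of the protocol article, under Sample size calculation. It has three steps.

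1. A G*Power repeated-measures calculation gives the "total number of participants predicted to show measurable change in cognition required to obtain power = 0.80", the result being described as one "which is 200 using the repeated measures algorithm". The printed inputs include "alpha = 0.05, 2 groups (Change, No-Change), 12 repeated measures" and "a correlation between measures of 0.5".
2. Because 52.1% of participants are expected to change over three years, "a total sample of 384 participants is required".
3. For losses, "a 20% attrition rate [16] was used to calculate the total number of participants to be enrolled in this study", and the paragraph ends: "This resulted in a total required sample of 460".

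The article gives no other definition of the 20% and does not describe replacing participants who leave.

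**The concern.** An attrition rate is the share of enrolled participants who are lost, so it applies to the enrolled number. To keep *n* participants after losing a share *d*, one enrols *n*/(1 − *d*). Multiplying *n* by (1 + *d*) is a common slip that always falls short, because the loss is then taken from the larger, inflated number. The printed 460 looks like the product of that slip.

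The enrolment target is the figure the study recruits to. Participants must attend four times a year for three years, and the Anticipated challenges section lists that commitment as a difficulty, so the attrition allowance matters in practice. A reader would take 460 to secure the 384 participants and 200 changers at a 20% loss. If it does not, the stated basis for the study size is wrong, however much or little power that costs.

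**Working it through.** **Inputs**, all from Sample size calculation: 200 changers, 52.1% expected to change, 384 required before the attrition allowance, 20% attrition, 460 to be enrolled.

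**Reproducing the plan's figures**

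- Required sample: 200 / 0.521 = 383.9, rounded up to 384. This matches.
- Enrolment by adding 20%: 384 × 1.20 = 460.8. This matches the printed 460 if the fraction is dropped; rounding up, as is usual for a minimum, would give 461.
- Enrolment by division: 384 / (1 − 0.20) = 480. This does not match 460.
- Rounding at the first step does not explain the gap. Carrying 383.877 forward gives 460.7 by multiplication and 479.8 by division.

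So 460 comes from multiplying by 1.20.

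**What each enrolment leaves at 20% attrition**

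| Enrolled | Retained (× 0.80) | Expected changers (× 0.521) |
|---|---|---|
| 460 | 368 | 191.7 |
| 461 | 368.8 | 192.1 |
| 480 | 384 | 200.1 |

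**Size of the gap**

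- Enrolled: 480 − 460 = 20, and 20/480 = 4.2%.
- Retained: 384 − 368 = 16, and 16/384 = 4.2%.
- Changers: 200 − 191.7 = 8.3, about 8.
- Attrition at which 460 still leaves 384: 1 − 384/460 = 16.5%.

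**Effect on power**

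This depends on how the 200 is read. I used the noncentral F for the between-groups test with N subjects, m = 12 measures, ρ = 0.5, two groups and α = 0.05. The noncentrality is λ = f²·N·m / (1 + (m − 1)ρ), where the denominator is 1 + 11 × 0.5 = 6.5.

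- *The 200 taken as giving exactly 80% power.* The implied effect size is f = 0.147. At N = 192, power is about 78%.
- *Effect size taken as f = 0.17.* The article prints a garbled value with two decimal points, so 0.17 is an assumption. Then 150 subjects suffice for 80% power, 200 give about 90%, and 192 give about 89%. The within-subject and interaction tests need only about 26.

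The second reading shows that the printed inputs, with f = 0.17, do not give 200 at 80% power. No loss of power below the target can therefore be asserted from the article.

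**The case against.** The arithmetic is hard to dispute; the case on the other side is that it matters little.

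- *The gap is small and the assumptions are soft.* About 4% of the sample is at stake, and 460 is enough for any attrition up to 16.5%. The 20% is a planning value from a cited source, and the 52.1% is an average over three age bands, so a different age mix could move the number of changers as much. This is true and limits the practical effect, but it does not make the printed figures agree.
- *No real loss of power is shown.* This stands. Depending on the reading, 192 changers give about 78% or about 89%. If the 200 is instead the total over both groups, as the two-group input may suggest, 368 participants exceed it comfortably. The point here is about the enrolment arithmetic and makes no claim on power.
- *The 384 is not expressly labelled as a number after attrition.* That is so. But it is derived before the attrition step, and the allowance is then applied to it, so the natural reading is the number the study needs to have left.
- *The 20% may have been meant as a mark-up on 384.* The article calls it an attrition rate. A 20% mark-up covers attrition of only 1 − 1/1.20 = 16.7%, so on that reading the rate is misreported.
- *Participants who leave still contribute data.* The mixed model under Predictive modeling phase can use visits made before leaving, so the effective loss may be below 20%. However, someone who leaves early may not be observed to change, and the article does not use this argument to justify 460.

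**Conclusion.** The concern holds. The requirement of 384, the attrition rate of 20% and the enrolment of 460 cannot all be right together. At 20% attrition, 460 leaves 368 participants and about 192 changers: 16 and about 8 fewer than stated. The enrolment consistent with the plan's own figures is 480.

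This rests on two readings of the text: that the 20% is a share of those enrolled, and that 384 is the number needed once losses have occurred. Both are the ordinary meaning, and nothing else in the article points elsewhere. The conclusion is confined to the enrolment figure, which is wrong as written whatever the power turns out to be.

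**What to change.** Correct the last step of the Sample size calculation section in one of two ways.

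- State the attrition-adjusted enrolment as 384/0.80 = 480. If this becomes the recruitment target, it means 20 more participants.
- Keep 460 and state that at 20% attrition it yields 368 participants and about 192 expected changers, with power given for those numbers. This costs one sentence and no extra recruitment.

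In either case, 460 should not be presented as meeting a requirement of 384 at 20% attrition. Giving power under the second option requires a legible effect size and a statement of which G*Power test was used, so those should be settled in the same edit.
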